## Abstract

**Background:**

Attention-deficit/hyperactivity disorder (ADHD) in adulthood, with an estimated prevalence of 2–3%, is associated with several challenges in daily life functioning. The availability of evidence-based psychological interventions for adults with ADHD is still poor. Interventions delivered over the Internet on smartphones or personal computers may help to increase the availability of effective psychological interventions. The primary aim of this randomized controlled trial is to examine the efficacy of a self-guided Internet-delivered intervention on severity levels of ADHD symptomatology and quality of life.

**Methods:**

We aim to include 118 participants with a self-reported ADHD diagnosis in a randomized controlled trial with two arms: 1) self-guided Internet-delivered intervention for coping with ADHD (*N* = 59); 2) self-guided online psychoeducation (control group, N = 59). After 3 months, the control group will be given access to the intervention. The primary clinical outcomes are inattention and quality of life. Secondary clinical outcomes are hyperactivity, stress and depression. Measures will be obtained at three time points: before (baseline), immediately after (8 weeks) and 3 months after the intervention. Uptake, usage, adherence and satisfaction will be explored.

**Discussion:**

This RCT will provide valuable information on the clinical effectiveness of an Internet-delivered intervention for adults with ADHD. This study is, to our knowledge, one of the first randomized control trials that investigates the effects of a self-guided Internet-delivered psychological intervention in a fairly large group of adults with ADHD.

**Trial registration:**

ClinicalTrials.gov, Identifier NCT04726813, January 27, 2021.

## Introduction

1

Attention Deficit Hyperactivity Disorder (ADHD) is a neurodevelopmental disorder characterized by pervasive symptoms of inattention and/or hyperactivity/impulsiveness that persist across different situations (Edition, 2013). Longitudinal studies have shown that at least 60% of children diagnosed with ADHD will continue to show symptoms into adulthood with a severity level that requires treatment (Faraone et al., 2006; Franke et al., 2018; Kessler et al., 2005a). With an estimated prevalence as high as 2–3%, ADHD is a common disorder in adulthood.

It is important to provide effective treatment to adults with ADHD, as the disorder is associated with problems related to the regulation of behaviour, cognition and emotions and often causes a wide range of challenges in daily life functioning (Franke et al., 2018). Availability of appropriate psychological interventions for adults with ADHD should thus have a great impact on the daily life functioning at an individual and societal level.

Pharmacological treatment is commonly a first choice of treatment for adults with ADHD. Although effective on a group basis, it is acknowledged that many show intolerance to medication, lack of response or residual impairments and/or side effects such as reduced sleep and appetite (Spencer et al., 2000). Due to this, non-pharmacological treatment options are increasingly demanded by adults with ADHD (Solberg et al., 2019; Vidal et al., 2013).

Increased availability and use of non-pharmacological treatment options are part of official policy (Nutt et al., 2007; Gibbins and Weiss, 2007), but so far, psychological treatments for ADHD are still not widely available in routine clinical practice. Few adults with ADHD are offered psychological treatment following completion of neuropsychiatric assessment and diagnosis, even though long-term studies have underscored its importance (Kooij et al., 2019).

Several psychological interventions are developed for, or adapted to, adults with ADHD in the recent years. Although the evidence base for psychological treatment is still relatively limited, some recent studies based on cognitive behavioral therapy (CBT) (Knouse and Safren, 2010; Anastopoulos et al., 2021; Weiss et al., 2008; Weiss et al., 2012) and dialectical behaviour therapy (DBT) (Hesslinger et al., 2002; Hirvikoski et al., 2011) have shown promising results, both when it comes to reducing ADHD related symptoms and increasing life quality. The focus in these treatments is to enhance executive and organizational skills, improvement of consequence thinking and impulse control as well as emotion regulation skills. Other interventions like goal management training (GMT), have also been investigated as treatment options for adults with ADHD (Dymphie et al., 2017; Braek et al., 2009; Nordby et al., 2021; Jensen et al., 2021). As executive functions, like goal-directed and context appropriate behaviour, are often impaired in adults with ADHD, GMT teaches participants strategies for stopping unwanted behaviours, improving planning of activities and structuring intentions.

In sum, most treatment guidelines to date recommend a combination of pharmacological and non-pharmacological treatment options for adults with ADHD, given that a significant number cannot tolerate, do not respond to, or fail to reach optimal results with medication alone. Psychological interventions like CBT, GMT and DBT for ADHD provide new, compensatory strategies and skills for deficient attention, executive functioning, impulse control and emotion regulation, but they are often not available to adults with ADHD due to barriers such as: limited resources, lack of knowledge and qualified therapists, and other factors such as geographical distance and stigma (Solberg et al., 2019; Weiss et al., 2008).

### Internet-delivered interventions for adults with ADHD

1.1

Psychological interventions delivered over the Internet may help to overcome these barriers. They have the potential to offer treatment outside of the traditional treatment centres, reach individuals in regions where psychological treatment is not available and offer more flexibility for the patient (Andersson, 2016). Internet-delivered interventions can also provide a cost-effective opportunity to provide 24-h access to information, advice and support. These interventions can be provided with therapist support, so called guided Internet-delivered interventions, or without therapist support, so called self-guided Internet-delivered interventions. Self-guided Internet-delivered interventions often provide daily support in the form of automatic reminders, feedback regarding progress, overcoming obstacles and help with planning daily activities (Titov et al., 2014). These type of interventions can help managing symptoms of ADHD by providing general information, tailored advice, support and skill training via technology (e.g. smartphones, tablets or websites) (Andersson and Titov, 2014). Internet-delivered interventions are expected to be appropriate for adults with ADHD who have insufficient response to medication, who are in need for an add-on treatment option, and/or prefer non-pharmacological treatment options. Some individuals with an ADHD diagnosis already use timers, schedules and reminders, tools that are available on their smartphones (Moëll et al., 2015). However, there is a lack of controlled studies investigating whether self-guided Internet-delivered interventions contribute to improved daily functioning for adults with ADHD.

### Objectives

1.2

The primary objective of this study is to evaluate the effects of a self-guided Internet-delivered psychological intervention on i) symptoms of inattention and quality of life in adults with ADHD, and ii) symptoms of hyperactivity, stress and depression. These effects will be compared with results obtained in a group of adults with ADHD randomized to a psychoeducation control condition. The secondary objective of the study is to explore user satisfaction with and adherence to the intervention.

### Trial design

1.3

The planned study will use a randomized controlled trial (RCT) design with two arms, 1) a self-guided Internet delivered psychological intervention, 2) an Internet-delivered psychoeducation control condition. We hypothesize that the psychological intervention is superior to psychoeducation. The study will include two follow-up assessments, at 8 and 12 weeks after baseline measurements to assess longer term effects of the intervention.

## Methods

2

### Study setting and design

2.1

The responsible study center is located at the University of Bergen, Norway. All data will be collected using online questionnaires and telephone interviews. Data will be collected from eligible participants in Norway. Participants will be recruited via social media and the Norwegian ADHD organization.

This randomized controlled trial has two arms: arm I is a self-guided Internet-delivered intervention (MyADHD), arm II is a psychoeducation control. Due the nature of the intervention and the comparison, it is impossible to blind people to the condition.

### Eligibility criteria

2.2

Adults (≥18) with a self-reported ADHD diagnosis are eligible to participate in the study. Participants will be screened for inclusion and exclusion criteria before randomization.

Criteria for inclusion:a)Age ≥18b)A self-reported diagnosis of ADHD (date, venue and diagnosing physician)c)Access to and ability to use a computer, smartphone and the Internet.d)Current self-reported problems with organizing daily activitiese)Participant is by investigators considered able to follow through the intervention protocol and take part in assessment measuresf)Speaks, writes, and reads Norwegiang)Participant who is taking prescribed ADHD medication has to be stable on the medication at least four weeks before the study and during the timespan of the study.

Exclusion criteria:a)Current self-reported diagnosis of severe psychiatric illness such as borderline or antisocial personality disorder, bipolar disorder,b)Ongoing substance abusec)Ongoing suicidal ideation assessed with item 10 on the Montgomery Aasberg Depression Rating Scale (Fantino and Moore, 2009)d)Ongoing engagement in another psychological treatment

### Informed consent and withdrawal from the study

2.3

Participants who are eligible to participate in the study, as assessed by a pre-screening questionnaire and a follow-up telephone interview, will have to sign a consent (see questionnaires and participant timeline section). The consent will be signed digitally in a secure portal with BankID (level 4 protection). Participants can end their participation at any time and for any reason. In addition, should the condition of a participant deteriorate, supervising clinicians may choose to end the participation prematurely and direct the participant to official health care services.

### Intervention

2.4

#### MyADHD Intervention description and development

2.4.1

The intervention will be delivered via an online secure portal, which is accessible on smartphones, laptops and personal computers. The intervention is a short-term, structured self-guided intervention with modified elements from CBT, DBT and GMT to target specific challenges experienced by adults with ADHD. As ADHD in adulthood affects many psychosocial domains, we expect that a combination of therapeutic techniques from various psychotherapeutic frameworks that already have been examined and have shown promising effects in face-to-face and group therapy, might be more beneficial to adults with ADHD than focusing on one treatment framework alone. CBT for adults with ADHD includes behavioral interventions targeting the practice of compensatory skills and cognitive interventions targeting negative thoughts, avoidance and procrastination. Strategies include prioritization, organization, problem solving and stress management. DBT strategies include emotional regulation, impulse control, self-regulation, self-esteem and self-acceptance (Swales and Heard, 2016), while GMT has a stronger focus on inhibitory control (Stamenova and Levine, 2019). By combining treatment frameworks, it is possible to tailor the intervention to key concern and difficulties reported by adults with ADHD, as shown in a recent publication from our research group (Flobak et al., 2021).

The creation of the content of the modules was done by using the Person-based approach (Yardley et al., 2015) and included: consultation with experts and members of user groups; examination of relevant theory and evidence from previous trials and treatment manuals. The intervention has been iteratively modified for optimization from user perspective. We held several focus group meetings with *N* *=* 12 adult participants with ADHD, and a lived-experience workshop with *N* = 11 adults with ADHD. In the lived experience workshop, we interviewed participants about their experiences with coping with ADHD. This information formed the content of the videos, which are included in the intervention. In the videos, an actor plays out the lived experience in one video (e.g., problems with attention) and in the second video, an actor plays out the coping strategies (Flobak et al., 2021). A pilot study has been performed and shown promising results (Nordby et al., 2021).

The intervention consists of seven training modules that are released weekly for the intervention group participants. The main goals of the intervention are to help participants to obtain improved functioning in daily life activities; offer strategies that will lead to stress reduction, reduce inattention and improve quality of life. The intervention includes: a short introductory chapter (open to everyone), followed by a start module (goal setting) and six different themed optional modules. A brief overview of modules content is shown in Table 1. Each module includes psychoeducation alongside text, audio and video material instructing participants in the use of specific techniques. Participants will be encouraged to complete weekly action plans and symptom questionnaires for each module. Further, modules include case vignettes and lived-experience videos serving to clarify important training principles and help participants make connections between the material and their own experiences. Automatic reminders are sent when a participant does not log on within one day after release of a new module, or not finishes a module within 4 days. Homework is given after modules 2–6, where the participants are asked to continue training in everyday situations on the newly learned skills and to log situations in which the participants succeeded or failed.

**Table 1 t0005:** Overview of the intervention in Arm I.

Module^a^	Rationale and content
Obligatory modules	
Information module	Information about the study
1. Start module	Goal setting and practical information about how to use the Internet-delivered intervention.
2. Mindful awareness	Inattention is a core symptom of ADHD. In this module, participants are given information about different aspect of attention and concentration and how to cope with impairment. In this module the participants start training on mindful awareness (“being here and now”) by focusing on their breathing. *Based on DBT*.
3. Inhibition training	Impulsivity and loss of impulse control are common among adults with ADHD. This module consists of exercises focussing on impulse control and goal oriented-directed behaviour (stop, observe, proceed, check). *Based on GMT*
4. Emotional regulation	Emotional instability and brief recurrent states of feelings are common in ADHD. In this module, participants are first informed about modern theories of emotion (primary emotions, relationship cognition-emotion and emotion-behaviour) and then presented exercises to improve emotional analysis (emotions record, emotion diary) and emotional regulation. *Based on DBT*.
5. Planning and organizing daily life	Problems with planning an organizing sequential behaviour often result in situations where adults with ADHD do several different things at the same time, feel pressurized, and end up finishing none of their planned tasks. Adults with ADHD often feel that this behaviour is a result of emotional stress and experience this deficit as stressful in itself. This module presents stress management techniques, how to handle a tendency towards procrastination, breaking down large tasks. *Based on CBT*.
6. Self-acceptance	In this module the focus is on accepting what one cannot change and to be kind to oneself. Psychoeducation about understanding how actions are separate from ones qualities, identifying and acknowledging strengths, practice forgiveness. The goal is to enhance self-compassion. *Based on DBT*.
7. Summary and road ahead	Summary of all the modules and planning for the future

a Features common across all modules: automatic reminders, (homework) exercises, downloadable hand-outs, weekly questionnaires, progress graphs, lived-experience videos.

#### Psychoeducation control

2.4.2

Participants in the control condition will be assigned to psychoeducation modules (see Table 2) and will receive restricted access to the platform. They can contact or be contacted by the research team if their symptoms levels increase.

**Table 2 t0010:** Overview of the psychoeducation control in Arm II.

Module	Rationale and content
Modules	
Information module	Information about the study
Psychoeducation	Prevalence, etiology, symptom description, general advice and strategies for coping with ADHD. Links to patient information websites and apps for mobile phone (calendar, planner etc).

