### Criteria for discontinuing or modifying allocated interventions

2.5

Key stopping rules for patients are a withdrawal of informed consent or unwillingness to further participate in the trial or any factors affecting the patient's well-being. When participants score above 20 on the PHQ-9; express suicidal ideation (a score MADRS-SR ≥ 4); or write concerning messages in the open text fields, they will be contacted by the research team for a screening. Based on clinical evaluation it will be decided whether a participant should continue the intervention.

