### Outcomes

2.6

All outcome questionnaires are self-report scales that participants themselves can fill out via an online secure platform. Assessments are repeated at baseline, 8 weeks, and 12 weeks. An overview of the measurements is giving in Table 3.

**Table 3 t0015:** Questionnaires and measures.

	Screening	Baseline	Weekly in intervention a	8 week post-test	3 M follow up
Eligibility criteria					
Diagnosis of ADHD (self-report) - Date - Venue - Diagnosing physician	x				
Access to pc, smartphone or laptop with Internet connection	x				
Understands Norwegian	x				
Current stable use of ADHD medication (self-report) - Yes - No - Type	x				
Ongoing substance abuse (self-report)	x				
Self-reported severe mental illness such as borderline or antisocial personality disorder, bipolar disorder and/or mental retardation	x				
Currently receiving psychological treatment for ADHD	x				
Availability for the next 4 weeks	x				
MADRS-SR (item 10; suicidality)	x	x		x	x
Demographic variables questionnaire - Gender - Age - Educational level - Occupational status - Personal contact information (email, telephone number) - Postal code	x	x			
ASRS		x	x	x	x
AAQol		x		x	x
PHQ-9		x		x	x
GAD-7		x		x	x
PSS		x		x	x
Changes in medication and engagement in other therapeutic interventions questionnaire		x		x	x
Self-report adverse events				x	x

Usability measures					
Use, benefit and understanding of the modules components (questionnaire specifically design, open questions)			x		
CEQ		x		x	x

Participant-generated data					
User login Completed modules Completed questionnaires Completed homework Completed assignments Time spent on reading material Time spent on module/exercise Clicks			x	x	x

Content evaluation					
Participant feedback within the program			x		

a These measures will only be filled out by the intervention group. AAQOL-29: Adult ADHD Quality of Life Scale. ASRS: the adult ADHD self-rating scale. CEQ: credibility and expectancy scale. MADRS: Montgomery And Åsberg Depression Rating Scale. MADRS SR: Montgomery And Åsberg Depression Rating Scale Suicide Rating. PHQ-9: patient health questionnaire 9. PSS: perceived stress scale.

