*Step 6*: *Internet-delivered intervention/control*. Participants assigned to the intervention group will start the Internet-delivered course immediately for 8 weeks, whereas the control group participants will start with the psycho-education module and receive access to the adaptive version of the intervention after 3 months. Participants will receive automatic reminders (text messages) when they are inactive in the intervention (defined as not logged in 1 days or not finished a module within 4) and will receive automatic reminders at the post-intervention and at the 3-month follow-up time points to encourage them to complete their assigned tasks and questionnaires.

*Step 7*: *Control groups receives the intervention*. Participants assigned to the control group will receive access to the intervention after 3 months. For intervention group participants, the participation is complete (Fig. 1).

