### Limitations

3.2

The current study has some limitations. First, the outcome measures are based solely on self-reports which may be subject to reporting bias, although rating scales are shown to reliably, validly and efficiently measure DSM-based ADHD symptoms in adolescent samples (Collett et al., 2003).

Second, the research study excludes those with signification personality disorders, current substance use, suicidal ideation, and other severe psychiatric problems although these patients represent a significant proportion of the population of adults with ADHD. However, since this is an entirely self-guided intervention, we needed to take these safety issues into account.

A final limitation of this study includes our sample of convenience, which may inadequately represent the full population of adults with ADHD (e.g., adults with comorbidities).

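### The PHQ-9 and MADRS-SR triggers in section 2.5 are not measured between baseline and week 8, so they cannot detect worsening during the MyADHD course, and controls have no scheduled symptom data in that window

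*Protocol article*

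**What the plan says.** **The rule.** Section 2.5, on discontinuing or modifying the allocated interventions, names three events that lead the team to contact a participant for screening: "When participants score above 20 on the PHQ-9; express suicidal ideation (a score MADRS-SR ≥ 4); or write concerning messages in the open text fields". It then says: "Based on clinical evaluation it will be decided whether a participant should continue the intervention". The rule is not limited to one arm.

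**Controls.** Section 2.4.2 says: "They can contact or be contacted by the research team if their symptoms levels increase". It names no instrument, threshold or time.

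**The schedule.** Section 2.6 says: "Assessments are repeated at baseline, 8 weeks, and 12 weeks". Table 3 agrees for PHQ-9 and MADRS-SR item 10, adds screening for item 10, and leaves the weekly cell empty for both. The only symptom scale marked weekly is the ASRS. Footnote a to the weekly column reads: "These measures will only be filled out by the intervention group".

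**The course.** Section 2.7.1, Step 6: "Participants assigned to the intervention group will start the Internet-delivered course immediately for 8 weeks". Step 7: "Participants assigned to the control group will receive access to the intervention after 3 months".

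**The concern.** A rule that decides whether someone stays on an intervention is most useful while the intervention is running. Two of the three triggers are questionnaire scores, and after baseline these are next collected when the MyADHD course ends. A MyADHD participant who crosses a threshold in weeks 1–7 would not be picked up by score until then. A crossing that resolves before week 8 would never be seen by score.

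For controls, the team can act on an increase in symptoms only if it learns of one, and no symptom data are scheduled for them between baseline and week 8.

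What is at stake is participant safety, and whether the article describes accurately how participants are watched. The authors give the format as a reason for caution when they explain their exclusions in section 3.2: "since this is an entirely self-guided intervention, we needed to take these safety issues into account". With no therapist in routine contact, the scheduled measures carry more of the load.

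**Working it through.** The plan states no figure on this point, so the check sets the rule against the schedule, row by row.

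**Step 1. Scheduled collection (Table 3 and its footnote a).**

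| Measure | Screening | Baseline | Weeks 1–7, MyADHD | Weeks 1–7, control | Week 8 | 3 months |
|---|---|---|---|---|---|---|
| PHQ-9 (2.5 trigger) | no | yes | no | no | yes | yes |
| MADRS-SR item 10 (2.5 trigger) | yes | yes | no | no | yes | yes |
| Open text (2.5 trigger) | no | no | yes | no | no | no |
| ASRS (not a trigger) | no | yes | yes | no | yes | yes |
| GAD-7, PSS (not triggers) | no | yes | no | no | yes | yes |
| Self-reported adverse events | no | no | no | no | yes | yes |

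Section 2.4.1 mentions symptom questionnaires with each module. Table 3 shows these can only be the ASRS, which no 2.5 trigger uses.

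**Step 2. Count the triggers with a scheduled source between baseline and week 8.**
- Score triggers: 0 of 2 in MyADHD and 0 of 2 in controls.
- All three triggers: 1 of 3 in MyADHD (open text) and 0 of 3 in controls.

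**Step 3. Where the score triggers can act.**
- *Baseline, both arms.* Randomization is Step 4, the baseline questionnaires are Step 5 and the course is Step 6. A baseline crossing is therefore seen after allocation with the whole course ahead. Table 3 does not list PHQ-9 at screening, so this is a real decision point.
- *Week 8, MyADHD.* The course has just ended, so nothing is left to discontinue.
- *Week 8 and 3 months, controls.* Access to MyADHD comes after 3 months, so both scores fall before or at that point and can inform whether the delayed course should start.

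**Step 4. Length of the gap.** With the last assessment at week 12, as in sections 1.3 and 2.6, the interval without score triggers is 8 of 12 weeks: 8/12 = 67%. In MyADHD it covers the whole course.

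**Step 5. Illustration only.** Suppose crossings are spread evenly over weeks 0–8 and persist. The mean wait until the week-8 score is 8/2 = 4.0 weeks. With a further check at week 4 it is 4/2 = 2.0 weeks. These values follow from the assumed timing and are not evidence about this trial. The documents give no crossing rate, so no number of affected participants is offered.

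**The case against.** The strongest reply is that the documents do not contradict themselves. Section 2.5 promises no mid-course scoring. It says what happens when a score is high, which is consistent with scheduled assessments. Section 2.3 lets supervising clinicians end participation if a participant deteriorates, and section 2.5 lists well-being more generally as a reason to stop. Neither is tied to a visit. Participants can write in, and MyADHD participants have weekly open text. An article may also leave safety operations to the full protocol.

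Much of this stands and limits the point. Clinician discretion and participant-started contact are real safeguards in weeks 1–7, but they depend on the participant making the worsening known. The appeal to a fuller protocol is weaker. The article prints both the rule and a complete schedule, with a weekly column that is filled for the ASRS and empty for the two safety measures.

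Three stronger readings are tempting and not supported:
- *The stopping rule cannot act in time in either arm.* It can act at baseline in both arms. For controls, the week-8 and 3-month scores still precede or coincide with the decision on delayed access.
- *Section 2.4.2 depends on questionnaire scores.* It names none and it allows contact started by the participant. The gap concerns only contact started by the team, which has no scheduled data to prompt it before week 8.
- *Unequal monitoring biases the treatment comparison.* Nothing in the documents shows this, and it is not claimed.

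**Conclusion.** The point holds as a gap in safety monitoring. Between baseline and week 8 neither section 2.5 score is collected in either arm. In MyADHD the score triggers therefore cannot detect worsening during the 8-week course, which leaves open text, participant-started contact and clinician discretion. In controls the same window has no scheduled symptom score and no open-text item, so team-started contact under section 2.4.2 has nothing scheduled to act on.

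These conclusions rest only on Table 3, its footnote and the step order in section 2.7.1. The 67% also rests on reading the follow-up as week 12. How many participants would be affected cannot be derived from the documents. The gap is worth closing because the remedy is cheap.

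**What to change.** Add PHQ-9 and MADRS-SR item 10 once mid-course in both arms, and apply the section 2.5 triggers to them. Week 4 is the midpoint of the course and a reasonable choice, though the documents do not dictate it. Include the controls' delayed course where it has not yet started. Leave all existing safeguards in place.

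The trial status section says that recruitment is finished and the second group is completing the course, so the schedule can change little for this trial. For participants already past mid-course, report contacts and clinician-ended participation by arm, and state that the score triggers were not measured mid-course.

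**Cost.** Ten items (9 + 1) per administration on the existing online platform. One administration in both arms is at most 118 short forms. Repeating it in the controls' delayed course adds at most 59, giving 118 + 59 = 177. Some screening calls would come earlier, and there would be a few more for crossings that would have resolved unseen. There is slightly more contact in a trial meant to be self-guided, equally in both arms. No safety provision is removed and no extra participants are needed.
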